#### 3.2.2 Safety Endpoints

Change in laboratory safety variables, vital signs, physical examination from baseline and the incidence of adverse events, treatment emergent adverse events, serious adverse events during the trial.

#### 3.2.3 Secondary Endpoints

- a) Presence of bacteriuria at each visit up to week 26 of study
- b) Presence of leucocyturia at each visit up to week 26 of study
- c) Recurrent UTI episodes up to 6 months
- d) Urine proteomics
- e) Gene expression analysis
- f) DNA sequence analysis

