Clinical Trial Protocol

Interest in the use of anti-inflammatory drugs has increased in recent years, mainly in the form of NSAIDs, as an alternative to antibiotic therapy for uncomplicated cystitis with varying results [6]. The studies show that NSAIDs can be useful for treatments of acute symptoms and may slightly decrease recurrent cystitis, but due to a lack of specificity, these anti-inflammatory agents cannot completely replace antibiotics in the treatment of acute cystitis [7-9]. We believe that our strategy, to block the IL-1 receptor, has a much more precise and well-defined molecular mechanism as well as extensive support in experimental models.

Based on the research results described above, we want to evaluate the possibility of treating recurrent acute cystitis with Kineret. We want to investigate whether the treatment provides adequate cure for acute cystitis compared to conventional antibiotic treatment, both based on the patient's symptoms and inflammation and on the effects on bacteria in the urine.

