### 4.3 Subject identification and randomisation of treatment

All enrolled subjects will be randomized 2:1 to two study treatment groups at Visit 1.

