### **5.2 Inclusion Criteria for All Subjects**

1. Stable patients with an acute episode of recurrent uncomplicated cystitis.
2. Signed written informed consent form
3. Capability and willingness to comply with study procedures
4. Female subjects, 18 - 65 years old
5. Negative urine pregnancy test in women of childbearing potential.
6. Sum score of the main uUTI symptoms reported on the Acute Cystitis Symptom Score (ACSS) typical domain at visit 1 is  $\geq 6$
7. Typical symptoms must be acute, developed within  $\leq 6$  days
8. Historys of recurrent cystitis ( $\geq 3$  documented episodes in the history in the past year) or ( $\geq 2$  documented episodes in the history in the past 6 months))
9. Contraception

Contraception should be maintained during treatment and 30 days after last intake. Women of childbearing potential must use contraceptive methods which are considered as highly effective birth control methods. Such methods include:

- combined (estrogen and progestogen containing) hormonal contraception associated with inhibition of ovulation:
  - oral
  - intravaginal
  - transdermal

- progestogen-only hormonal contraception associated with inhibition of ovulation:
  - oral
  - injectable
  - implantable
- intrauterine device (IUD)
- intrauterine hormone-releasing system ( IUS)
- bilateral tubal occlusion
- vasectomised partner
- sexual abstinence

Hormonal contraception methods should be combined with barrier methods.

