### 5.3 Exclusion Criteria for All Subjects

1. Breastfeeding
2. Signs of pyelonephritis
3. Uncontrolled Diabetes Mellitus
4. Neutropenia ( $<1,5 \times 10^9/L$ )
5. Signs of genital infections (Vaginitis/ cervicitis)
6. Anamnestic exclusion of patients with active severe infections, history of viral hepatitis (only anamnestic exclusion possible, as immediate inclusion in the study is urgently required for this disease pattern. Serological and other blood test results (processing time  $\geq 24$  hours) cannot be waited for).
7. Patients using CYP450 medications (e.g. Warfarin, Phenytoin)
8. Patients using Phenytoin medication
9. Anamnestic exclusion of patients with a history of tuberculosis or active tuberculosis (only anamnestic exclusion possible, as immediate inclusion in the study is urgently required for this disease pattern. Serological blood test results (processing time  $\geq 24$  hours) cannot be waited for)
10. Extragenital conditions, nephrological conditions, urological conditions, urinary catheters that may lead to complicated UTI
11. Severe uncontrolled systemic disease
12. Systemic Antibiotic therapy within 5 days prior to inclusion
13. Impaired renal function (Creatinine clearance  $< 60$  ml /min)

14. Known allergies/contraindications to Kineret and Nitrofurantoin
15. Malign diseases
16. Immunosuppression
17. Previously enrolled in this trial
18. Pathological liver enzymes
19. Polyneuropathies
20. Glucose-6-phosphate dehydrogenase deficiency
21. Participation in other interventional clinical trials
22. Use of Diclofenac and Ibuprofen analgetic medication while participating in this clinical trial

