## 6.2 Description of Trial Visits

All procedures and assessments to be performed at each visit are detailed below and in the above study chart. All data will be recorded in the Patient's hospital notes or in a worksheet, as appropriate and be reported in the eCRF.

### Day 1

The subject will be considered for enrolment in the study, based on a diagnosis of cystitis. The investigator will explain the nature, purpose and risks of the trial and provide the subject with a copy of the Patient Information and Informed Consent. The patient will be asked to consider and evaluate participation in the study in accordance with the Helsinki Declaration and the local applicable laws. This visit is planned for all subjects independent of treatment arm.

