### 9.3.2 General Principles

Non-parametric and parametric methods will be used according to the properties of the data set. All confidence intervals will be presented with 95% degree of confidence.

An observed cases approach will be used for tabulations of data by visit (i.e. involving only those subjects who attended each specific visit).

The end of treatment values will be presented for laboratory parameters (primary and secondary endpoints) and for efficacy data.

For tabulations on changes from baseline, baseline will be defined as the last assessment performed before application of Kineret.

Categorical data will be summarised using the number and percentage of subjects in each category. Continuous data will be summarised using the mean, 95% confidence interval for mean (CI), standard deviation (SD), median, minimum and maximum values.

Any changes from the statistical analysis planned in this clinical trial protocol will be described and justified in a protocol amendment and/or in the clinical trial report dependent on the type of deviation.

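### Bacteriuria is assessed as presence at each visit in all entrants although entry needs no positive culture, so women sterile at Visit 1 shrink the absolute between-arm difference

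*Protocol*

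**What the plan says.** **Aim.** Protocol 2.1 wants to know whether Kineret gives adequate cure compared with conventional antibiotic, "both based on the patient's symptoms and inflammation and on the effects on bacteria in the urine".

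**Entry.** In 6.2 (Day 1), "The subject will be considered for enrolment in the study, based on a diagnosis of cystitis". Section 5.2 asks for "Stable patients with an acute episode of recurrent uncomplicated cystitis" and for a "Sum score of the main uUTI symptoms reported on the Acute Cystitis Symptom Score (ACSS) typical domain at visit 1 is" at least 6, with onset within 6 days and a documented history of recurrence. Neither 5.2 nor 5.3 requires a positive culture, a colony count or a positive dipstick.

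**Timing.** Section 4.3 states: "All enrolled subjects will be randomized 2:1 to two study treatment groups at Visit 1". The Visit 1 list in 6.2 includes the first bacterial culture. Where 5.3 explains why slow blood results are not awaited, it says that "immediate inclusion in the study is urgently required for this disease pattern". No section makes randomisation wait for the culture.

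**Endpoint and analysis.** Section 3.2.3 (a) is "Presence of bacteriuria at each visit up to week 26 of study". The full analysis set in 9.2 is all enrolled subjects who meet the eligibility criteria, and no culture-positive set is defined. Section 9.3.2 adds: "An observed cases approach will be used for tabulations of data by visit", restricted only by attendance at the visit.

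**The concern.** The scientific question is whether IL-1 receptor blockade clears bacteria as an antibiotic does. Presence of bacteriuria among all entrants answers that question only for those who had bacteriuria to begin with. A woman whose Visit 1 urine is sterile will usually contribute a negative result on Day 2, Day 5 and at Visit 6 under either treatment. Such women bring the two arms closer together on the absolute scale, which is the direction of similarity to the antibiotic that section 2.1 asks about. With 20 and 10 patients, the share of culture-negative entrants can also differ noticeably between arms by chance, and a reader of the all-patient table alone could not tell how far that explains the result. The Day 5 symptom comparison has a related weakness: it mixes infected women with women in whom the antibiotic has no organism to act on.

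**Working it through.** **Inputs from the protocol.** 20 patients on Kineret and 10 on nitrofurantoin (4.2). Cultures are taken in both arms at Visits 1, 2, 5, 6 and 7; those at Visits 3 and 4 are in the Kineret arm only (6.1). The protocol gives no culture-negative share and no bacteriuria rate.

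**The plan's own figure.** Section 9.3 cites 90% power at one-tailed alpha 0.05 with a paired t-test on change in symptom score. It gives no effect size or SD, so the figure cannot be reproduced; 90% power would need a standardised change of 0.68 with 20 patients and 1.01 with 10. It says that bacterial cultures informed the sample size but gives no number for them.

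**Assumptions.** A share q of entrants is culture-negative at Visit 1, with q from 10% to 40%. These women stay negative at the early visits. Among culture-positive women, bacteriuria persists in 40% on Kineret and 10% on nitrofurantoin (clearance 60% and 90%), a 30-point difference.

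**Step 1, dilution.** Observed presence = (1 - q) x persistence, so the observed difference = (1 - q) x 30 points.

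| q | Presence, Kineret | Presence, nitrofurantoin | Difference | Ratio of presence | Without bacteriuria |
|---|---|---|---|---|---|
| 0% | 40% | 10% | 30 points | 4.0 | 60% v 90% |
| 10% | 36% | 9% | 27 points | 4.0 | 64% v 91% |
| 20% | 32% | 8% | 24 points | 4.0 | 68% v 92% |
| 30% | 28% | 7% | 21 points | 4.0 | 72% v 93% |
| 40% | 24% | 6% | 18 points | 4.0 | 76% v 94% |

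The factor (1 - q) cancels from the ratio of presence. The ratio of absence moves towards 1, from 60/90 = 0.67 to 76/94 = 0.81.

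**Step 2, chance imbalance.** The difference between arms in the culture-negative share has SD = sqrt(q(1 - q)(1/20 + 1/10)).

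| q | SD of the difference in share | Chance of a gap of 20 points or more |
|---|---|---|
| 10% | 12 points | 13% |
| 20% | 16 points | 26% |
| 30% | 18 points | 33% |
| 40% | 19 points | 36% |

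This is imbalance in the share, not in bacteriuria itself. If persistence were 40% in both arms, a 20-point gap in share would produce 0.20 x 40 = 8 points of difference in presence.

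**Step 3, does restricting cost power?** Exact power of a two-sided Fisher test at 0.05. The full set is 20 v 10; the culture-positive subset is averaged over its random size. Each cell gives full set, then subset.

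| Persistence among positives | q = 0 | 10% | 20% | 30% | 40% |
|---|---|---|---|---|---|
| 60% v 10% | 74%, 74% | 66%, 69% | 56%, 59% | 43%, 50% | 28%, 41% |
| 70% v 10% | 87%, 87% | 81%, 86% | 73%, 79% | 62%, 70% | 46%, 61% |
| 50% v 20% | 27%, 27% | 23%, 25% | 19%, 19% | 13%, 16% | 8%, 13% |

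The subset has no less power than the full set in any cell, although at q = 30% it averages only 20 x 0.7 = 14 v 10 x 0.7 = 7 patients.

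**The case against.** The strongest reply is that this belongs in the SAP. The Synopsis and 9.3 defer the analysis to it, Visit 1 culture is collected in everyone, and nothing in the protocol forbids conditioning on it. That is true, and an unseen SAP may already do so. But the endpoint wording, the analysis sets and the by-visit rule are in the protocol, and together they describe an all-patient comparison. The SAP need only be final before database lock and the trial is open label, so a culture-positive subset first defined at that stage could be criticised as data-driven.

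A second reply is that entry is not as loose as it may sound. A history of documented episodes is needed, and 5.3 excludes genital infection and systemic antibiotics in the preceding 5 days. This stands as a reason to doubt the upper end of the 10% to 40% range, but none of these criteria confirms bacteriuria.

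Third, all entrants are a legitimate target when treatment starts before culture results, and over 26 weeks the endpoint also captures new bacteriuria, including in women who were sterile at Visit 1. This stands too, and is a reason to keep the all-patient table. Since these women have frequent recurrences, the assumption that they stay negative is plausible only for the early visits.

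A reader might infer that culture-negative women are scored as bacteriologically cured. The protocol has no cure or eradication category; they count as without bacteriuria. A reader might also infer a bias in favour of Kineret. Visit 1 culture status is fixed before randomisation, so its expected share is the same in both arms. What remains is chance imbalance, which is already part of the ordinary sampling error of the all-patient comparison. Nor does the protocol plan an equivalence or non-inferiority claim on bacteriuria; the comparability with antibiotic mentioned in 2.1 is an animal result.

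**Conclusion.** The point holds as dilution of a secondary endpoint. As the protocol stands, the absolute between-arm difference in bacteriuria at the early visits is reduced in proportion to the share of women who had none at entry: a 30-point difference becomes 27 to 18 points at shares of 10% to 40%. Both the difference and the shares are assumptions, as is the premise that women sterile at Visit 1 stay so at Visits 2, 5 and 6. The ratio of presence is not affected and no systematic bias is shown. Chance imbalance in the share has an SD of 12 to 19 points at 20 v 10, large enough that results should be shown by Visit 1 culture status. The definition of the primary endpoint is untouched. In a pilot trial this is a worthwhile, inexpensive improvement and not a flaw that invalidates the trial.

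**What to change.** Leave enrolment and visits as they are, and keep the all-patient table of bacteriuria at each visit up to week 26. Then:

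- State in 3.2.3 and 9.2 that the between-arm comparison of bacteriological effect at Visits 2, 5 and 6 is made among randomised patients with a positive pre-dose Visit 1 culture, or in all patients with adjustment for Visit 1 culture status.
- State that the Visit 1 urine sample is taken before the first dose, so that the subset is defined by a pre-treatment value. Section 6.10.3 already plans urine samples before and after treatment.
- Tabulate Visit 1 culture status by arm.
- Add a supportive analysis of the Day 5 ACSS change in the culture-positive patients.

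The cost is a few sentences and two tables from data already collected. The downside is fewer patients in the bacteriological comparison, about 14 v 7 at an assumed 30% share, without loss of power in the scenarios examined. Making the change before results by arm are known protects the subset from the charge of being chosen after the fact.

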|--------------------------------------------------------------|--------------------------------------------------------------------------------------------------------------------------------------------------------------------------------------------------------------------------------------------------------------------------------------------------|
| Investigational Product
Dosing
Administration | Kineret®
100 mg q.d. at Days 1,2,3,4,5
Subcutaneous injection                                                                                                                                                                                                                              |
| Control Medication
Dosing
Administration      | Nitrofurantoin Uro-Tablinen® (retard effect, 50 mg)
100 mg, two times per day over 5 days (adapted to patient weight – daily dose 3,6 mg/kg patient weight)
Oral                                                                                                                           |
| Primary Endpoint                                      | Reduction in symptom score measured by the ACSS in the first 5 days (ACSS dynamics)                                                                                                                                                                                                              |
| Secondary Endpoints                                   | 
 
• Bacteriuria at visits until 26 weeks
 
• Leucocyturia at visits until 26 weeks
 
• Recurrent UTI episodes until 6 months
 
                                                                                                       |
| Safety Endpoints                                      | Adverse event, treatment emergent adverse events, serious adverse events                                                                                                                                                                                                                         |
| Exploratory Efficacy Endpoints                        | 
 
• Urine proteomics
 
• Gene expression analysis
 
• DNA sequence analysis
 
                                                                                                                                                        |

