| Urine Proteomics                                                                                 | X                    | X                 |                                        | X                          |                      | X                          | X                  |
| Urine analysis culture (dip
slide, bacterial culture)                                         | X                    | X                 | X                                      | X                          |                      | X                          | X                  |

|                      | Screening
Visit 1 | Visits
2 and 5 | Visits
3 and 4                | Visit
6       | Safety Phone
Call | Visit
7 *      | Unscheduled visits |
|----------------------|----------------------|-------------------|----------------------------------|------------------|----------------------|-------------------|--------------------|
| Day           | Day
1             | Day
2 and 5    | Day
3 and 4                   | Day
15±2 days | Day 30               | Week
26±5 days |                    |
| Patients      | All patients         | All patients      | Only patients of
Kineret® Arm | All patients     | All patients         | All patients      | All patients       |
| Blood sample (RNA)   | X                    | X                 |                                  | X                |                      | X                 | X                  |
| Blood sample (DNA)   | X                    |                   |                                  |                  |                      |                   |                    |
| Urine Flow Cytometry | X                    | X                 |                                  | X                |                      | X                 | X                  |
| ACSS                 | X                    | X (on day 5)      |                                  | X                | X                    | X                 | X                  |

\* Final visit including Early Termination Visit (see below).

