#### Visits 2 and 5 Treatment Visits

Applicable to study patients of both treatment arms.

- Concomitant Medication
- Dispensing of Kineret®
- Adverse Events
- Vital Signs
- Blood sample (haematology and biochemistry)
- Urine analysis (RNA)
- Proteomics
- Urine analysis dip slide and bacterial culture
- Blood sample (RNA)
- Flow Cytometry urine sample
- ACSS (only on visit 5)

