#### Visits 3 and 4 Treatment Visits

Only applicable to study patients randomised to Kineret® treatment.

- Concomitant Medication
- Dispensing of Kineret®
- Adverse Events
- Vital Signs
- Blood sample for assessment WBC and differential for monitoring of neutrophils granulocytes (only on day 3)
- Urine analysis bacterial culture

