### 6.10.3 Urine Samples for efficacy

| Analyses       | Parameter                                                                                                                     |
|----------------|-------------------------------------------------------------------------------------------------------------------------------|
| Urine analysis | Bacterial culture

Leucocyte counts in uncentrifuged urine by flow cytometry

Dip slide for hematuria, leucocytes |

Prior to and after treatment, urine samples will be obtained and analyzed.

Routine analyses of urine samples (microbiology) will be processed at the microbiology laboratory of the Clinic and Polyclinic for Urology, Pediatric Urology and Andrology, Giessen. Urine status analysis (leucocyte counts) will be carried out at the central laboratory of the university hospital Giessen-Marburg, location Giessen. Urine dip stick tests (urine analysis) and urine culture analyses will be carried out laboratory of the Clinic and Polyclinic for Urology, Pediatric Urology and Andrology, Giessen. At the end of the clinical trial, parts of the samples are shipped to the laboratory at the Lund University, Sweden.

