## 9.3 Statistical Analysis

The statistical analysis will be specified in a Statistical Analysis Plan prior to Database lock. All data analysis will be based on statistical hypothesis testing. Population variables, adverse events and efficacy variables will be formally evaluated. The primary objective of the trial is to evaluate the safety and efficacy of Anakinra treatment for episodes of acute cystitis in patients with recurrent disease. No formal sample size calculation evaluating the power of the trial has been performed. However, a consideration regarding the sample size was made based on previous studies of Anakinra in a murine acute cystitis model. For efficacy, the sample size was based on analysis of symptom scores, inflammatory parameters and bacterial cultures. A sample size of 20 patients in the Anakinra treatment group and ten in the group receiving antibiotics was deemed suitable to achieve criterion for significance (alpha) 0.05 and power 90% using the paired samples 1-tailed t-test. The null hypothesis is H0: mean change in symptom score = 0 and the alternative hypothesis is HA: mean change in symptom score > 0.

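### Secondary endpoint 3.2.3 b fixes leucocyturia as present or absent although leucocyte counts are collected at baseline and four later visits in both arms; with 20 v 10 patients this can cost substantial power

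*Protocol*

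**What the plan says.** Section 3.2.3 b sets the endpoint as "Presence of leucocyturia at each visit up to week 26 of study". The synopsis is more open, "Leucocyturia at visits until 26 weeks", and would fit either a count or a yes/no result. No cut-off for presence appears anywhere, and no endpoint is defined as the count or its change.

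Section 6.10.3 lists, for efficacy, "Leucocyte counts in uncentrifuged urine by flow cytometry". It also lists a dip slide that reads leucocytes. The study chart in section 6.1 has a row "Urine Flow Cytometry" marked at Visit 1, Visits 2 and 5, Visit 6, Visit 7 and unscheduled visits. Section 6.2 agrees. Visits 2 and 5 include a "Flow Cytometry urine sample" and are "Applicable to study patients of both treatment arms"; Visits 6 and 7 are for all patients. Visits 3 and 4 are "Only applicable to study patients randomised to Kineret® treatment" and have no flow cytometry.

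Section 4.2 gives 20 patients on Kineret and 10 on nitrofurantoin. Section 9.3 says analysis will rest on hypothesis tests, that efficacy variables will be formally evaluated, and "For efficacy, the sample size was based on analysis of symptom scores, inflammatory parameters and bacterial cultures". It gives no effect size, SD or expected rate for any inflammatory measure.

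**The concern.** The rationale in sections 2.1 and 2.4 is that IL-1 blockade damps bladder inflammation, which is a matter of degree. If presence is read from the count, a patient whose count falls tenfold but stays above the cut is scored like one whose count did not move.

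Patients enter with acute cystitis. It is reasonable to expect, though the protocol gives no rate, that most have leucocyturia at Visit 1 and on Day 2, so a yes/no result may barely vary early in treatment. That argument is weaker at Visits 5, 6 and 7.

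At stake is one secondary comparison between arms of 20 and 10. A real difference could be missed in the stated endpoint although data able to show it will already have been collected.

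**Working it through.** **The plan's own figure.** Section 9.3 states 90% power at alpha 0.05 with a paired one-tailed t-test on change in symptom score. Solving the noncentral t distribution for 90% power gives a standardised change of 0.68 SD for n = 20 and 1.01 SD for n = 10. The protocol states neither an effect nor an SD, so its claim can be neither confirmed nor refuted. It also concerns a within-arm change in symptoms, so it says nothing about leucocyturia.

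**Inputs from the protocol.** 20 v 10 patients (section 4.2); alpha 0.05 (section 9.3, stated for the symptom score).

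**Assumptions, not in the documents.** Log10 counts are normal with equal SD in both arms. Kineret is lower by d SD, with d from 0.8 to 1.5. Tests are two-sided. The cut leaves a share p of controls present, with p from 30% to 90%.

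**Formulas.**
- Count: two-sample t-test, noncentrality = d × √(20 × 10 / 30) = 2.582 d, 28 df.
- Presence: the Kineret rate is Φ(Φ⁻¹(p) − d). Power is the exact binomial probability of all 2 × 2 tables that reject, by Fisher's two-sided test or by the uncorrected chi-square test.
- Example at d = 1.0, p = 50%: Kineret rate = Φ(0 − 1) = 16%. Power is 70% on the count, 45% by Fisher and 52% by chi-square.

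| d (SD) | t-test on count | Fisher on presence | Chi-square on presence | Loss, Fisher | Loss, chi-square |
|---|---|---|---|---|---|
| 0.8 | 51% | 12–31% | 18–38% | 20–39 | 14–33 |
| 1.0 | 70% | 27–45% | 34–54% | 25–43 | 16–36 |
| 1.2 | 85% | 42–61% | 52–69% | 23–43 | 16–33 |
| 1.5 | 96% | 51–81% | 66–86% | 15–45 | 10–30 |

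Losses are in percentage points. The ranges run over p = 30%, 35%, 50%, 65%, 70%, 80% and 90%. A finer grid over the same region gives the same extremes: 15 to 45 for Fisher and 10 to 36 for chi-square.

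**Baseline adjustment.** If the Visit 1 and later log counts correlate at 0.5 (assumed), the effective shift is d / √(1 − 0.25). With 27 df, power at d = 1.0 rises from 70% to 82%.

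**Smaller effects.** At d = 0.4, power on the count is only 17%. With p from 35% to 80%, the loss is 7 to 11 points (Fisher) or 3 to 9 (chi-square).

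**A different distribution.** Suppose patients divide into cleared and persistent groups, 3 to 6 within-group SDs apart on the log scale, with the cut midway. Control/Kineret presence was set at 30/80, 20/70, 80/30, 70/20 and 60/20%. In simulation (20,000 runs each), the t-test beats Fisher by only 2 to 11 points, and chi-square is 3 to 6 points above the t-test.

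**The case against.** **The presence result may not come from the count.** This stands in part. Section 6.10.3 also lists a dip slide that reads leucocytes, and presence is natural wording for such a test. The endpoint runs over each visit, yet flow cytometry is absent at Visits 3 and 4, where the study chart marks dip slide and culture. A reader might infer that the protocol derives presence by cutting the flow cytometry count; it does not say so. What remains is that the more informative count is collected for efficacy and is not the endpoint.

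**The SAP may analyse the counts.** It may, and section 9.3.2 allows laboratory values to be presented and parametric or non-parametric methods to be used. A reader might infer that the counts and each patient's baseline will go unused; the documents do not show that. Transformation, model and adjustment are SAP matters. The form of the endpoint is not: section 3.2.3 fixes it as presence, so a count analysis added later would not be the stated secondary endpoint.

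**The power loss depends on the model.** This stands. Under a clean split into cleared and persistent patients, which is plausible by the later visits, the loss is small or absent.

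**The stakes are low.** This also stands. Leucocyturia is a secondary endpoint in a pilot trial without a formal power calculation, and no success criterion depends on it.

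A reader might also infer that leucocyturia is the only non-exploratory measure of urinary inflammation. Section 3.2.3 does not support this: it lists urine proteomics and gene expression as secondary too, although section 3.2.4 repeats them as exploratory.

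**Conclusion.** The concern holds in a limited form. The protocol itself fixes the less informative version of an endpoint whose graded version will be collected in both arms at baseline and at Visits 2, 5, 6 and 7.

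Under a normal shift of 0.8 to 1.5 SD in log count, two-sided alpha 0.05 and control presence of 30% to 90%, the yes/no form gives up about 15 to 45 points of power with Fisher's test, or 10 to 36 with chi-square. These figures belong to those assumptions and are not a property of the design. The documents give no effect size or SD, the loss is under about 11 points near 0.4 SD unless the cut is extreme, and it can vanish if patients divide cleanly.

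The case for change is that the count risks little and may gain a good deal. Nothing here affects the primary endpoint, and the point does not extend to bacteriuria, because the protocol does not say how culture results are quantified.

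**What to change.** Reword 3.2.3 b, and align the synopsis, to: log10 urine leucocyte count by flow cytometry at Visits 2, 5, 6 and 7, compared between arms with adjustment for the Visit 1 log10 count. Use an ANCOVA at each visit or one repeated-measures model, with a rank-based version if the counts are badly skewed even after transformation.

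Keep presence of leucocyturia as a descriptive number and percentage. State whether it comes from the count or the dip slide, and give the cut-off.

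The cost is a line of protocol wording and the matching SAP text, with no new samples, visits or patients. The small downside is that a difference in log counts is harder to read than a percentage, which is why the percentage is kept.
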